## Study Product

TDF tablets are 300mg, light blue, almond‑shaped, film‑coated tablets for oral administration. Each tablet contains the following inactive ingredients: microcrystalline cellulose, lactose monohydrate, pregelatinized starch, croscarmellose sodium, and magnesium stearate. The film coating consists of lactose monohydrate, hydroxypropyl methylcellulose, titanium dioxide, triacetin, and FD&C blue #2 aluminum lake for color. Placebo tablets have an identical appearance to the TDF tablets and contain the inactive ingredients listed above and denatonium benzoate to provide a bitter taste to match the active tablets (Appendix 2). Gilead Sciences, Inc., will supply TDF and placebo tablets.

### Study Product Handling and Packaging

TDF or placebo tablets will be packaged at the Gilead manufacturing facility in white high-density polyethylene (HDPE) bottles. For the immediate arms, bottles will be packaged in kits of 7 bottles per participant. For the delayed arms, bottles will be packaged in 2 kits of 7 and one kit of 4 per participant. Each bottle will contain 30 tablets and a single silica gel canister to protect the product from humidity and fiber packing during handling and shipping. Study product should be stored before dispensing to participants at 25°C; excursions permitted to 15-30°C. Each bottle will be labeled with an identification number, the protocol number, administration instructions, expiration date, lot number, and sponsor address. Additional information will be included according to the protocol requirements and local law.

At the study sites, a designated staff person will transfer study product into another white HDPE fitted with a Medication Event Monitoring System (MEMS®) cap (52). Each bottle with the MEMS cap will be labeled with an identification number, the protocol number, administration instructions, expiration date, lot number, and sponsor address. Study product will be dispensed at enrollment, months 1 and 3 and then every 3 months thereafter for participants randomized to the immediate treatment arms. Participants randomized the delayed treatment arms will receive study product at 9, 10 and 12 months and then every 3 months thereafter. Participants will be instructed to return unused study product at each study visit. The investigator will be responsible for maintaining accurate records for all study bottles dispensed and returned. The inventory must be available for inspection by the study monitor. Study product supplies, including partially used or empty bottles and the dispensing logs, must be accounted for by the study monitor prior to destruction or return.

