## Randomization

Participants will be randomly assigned to one of the four arms: immediate study product receipt (TDF or placebo) or delayed study product receipt (TDF or placebo) in a 1:1:1:1 ratio. A CDC statistician will develop the allocation sequence using a permuted blocks randomization scheme. In a block of 8 study numbers, 2 assignments will be to immediate TDF, 2 to immediate placebo, 2 to delayed TDF, and 2 to delayed placebo. Randomization codes will be provided to Gilead Sciences, Inc., and study bottles will be labeled and filled with TDF or placebo using these codes and shipped to the appropriate site. Participants will be randomized to a group only after they have consented to participate and they have met the eligibility requirements for the study. Randomization will be stratified by study site. The list of treatment assignments and the assignment codes will be known only to the statistician and designated individual at Gilead Sciences, Inc., and only CDC will have access to the list of treatment assignments should the need for this information arise.

Group assignments will be concealed in sequentially numbered, sealed envelopes that will be distributed to each site by CDC and maintained in a secure location. After a participant has been properly enrolled in the study, a designated study staff member will obtain the next randomization envelope in sequence and be provided the information indicating the participant’s assignment to a delayed or immediate arm and the randomization number (bottle identification number) assigned.

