## Product administration

Each participant will be randomly assigned a unique ID number that corresponds to a pre-labeled, blinded, bottle of study product (TDF or placebo) tablets. At the enrollment visit for the immediate treatment arms and at the 9 month visit for the delayed treatment arms, participants will receive 37 tablets. They must return within 1 month after initial product receipt for a safety visit before receiving further study product. At the 1 month (immediate arm) and 10 month (delayed arm) visits participants will **have any returned pills re-dispensed and will** receive **an additional** 68 tablets. At subsequent quarterly visits, participants will receive 105 tablets.

Participants will be instructed to orally self-administer one tablet daily. The tablet should be swallowed whole. It is important to take the tablets regularly. Each dose should be taken as close as possible to twenty-four hours apart at the same time each day.

The participant will be counseled regarding signs and symptoms of toxicity and the importance of adherence. Two weeks and two months after the enrollment visit for the immediate arms and at 9.5 and 11 months for the delayed arms, participants will receive a phone call from study staff to assess any immediate problems. In addition, participants will be encouraged to call for any adverse experiences possibly related to study product, all serious adverse events, symptoms of acute retroviral infection or concerns regarding product adherence. Participants will be instructed to return unused study medication at each study visit and about the correct use of the MEMS® cap. Participants should not share or dispense study product to any other persons.

Dosage Modification

No modification of dosage will be allowed from this study. If a dose is forgotten, it should be taken as soon as remembered on that same day that it was missed. If a daily dose is missed, the participant should not double the dose the next day.

*Adherence Reminder Sessions*

Face-to-face adherence reminder sessions will take place at the initial product dispensing and each study visit thereafter. This session will include:

- The importance of following study guidelines for adherence to once daily study product
- Instructions about taking study pills including dose timing, storage, and importance of taking pills whole, and what to do in the event of a missed dose.
- Instructions about the purpose, use, and care of the MEMS® cap and bottle

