Should the investigator wish to assign the study records to another party or move them to another location, CDC must be notified in advance and give approval.

If the investigator cannot guarantee this archiving requirement at the study site for any or all of the documents, special arrangements must be made between the investigator and CDC to store these documents in sealed containers outside of the site in order that they can be returned sealed to the investigator in case of a regulatory audit. Where source documents are required for the continued care of the participant, appropriate copies should be made for storage outside of the site.

Case Report Forms (CRFs) and Source Documentation

For each participant screened, a CRF must be completed and signed by the study staff member administering the form. If a participant withdraws from the study, the reason must be noted on the CRF. If a participant is withdrawn from the study because of a treatment-limiting adverse event, thorough efforts should be made to clearly document the outcome.

Study Product Accountability

The study sites will receive a supply of study products (TDF and placebo) sufficient for the anticipated number of study participants. All supplies must be stored in a limited access area that is securely locked. For purposes of inventory accountability, the study sites will not make supplies of the study product available for distribution by any person not part of the study staff or provide these supplies to persons not enrolled in the study.

Each investigator or designee is responsible for ensuring adequate accountability of all used and unused study product. This includes acknowledgment of receipt of each shipment of study product (quantity and condition) and participant dispensing records. Dispensing records will document quantities received from Gilead and/or CDC and quantities dispensed to participants, including lot number, date dispensed, participant identifier number, participant initials, and the initials of the person dispensing the medication. All unused supplies of the study product must be furnished to CDC at the end of the study, or disposed of in a manner specified by CDC. Prior to return of used, unused and depleted containers, final drug accountability and reconciliation will be performed by the monitor.

All study drug supplies and associated documentation will be regularly reviewed and verified by the monitor.

Inspections

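### Kits packed differently by timing arm could show the next immediate or delayed assignment, because the protocol does not separate bottle numbers from envelope order

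*Protocol*

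**What the plan says.** **Packaging (5.3.1).** For the delayed arms: "For the delayed arms, bottles will be packaged in 2 kits of 7 and one kit of 4 per participant". For the immediate arms: "For the immediate arms, bottles will be packaged in kits of 7 bottles per participant"; the number of kits is not given. "Each bottle will contain 30 tablets".

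**Numbering and concealment (5.2).** The codes go to the manufacturer, and "study bottles will be labeled and filled with TDF or placebo using these codes and shipped to the appropriate site". Blocks are defined as sets of eight study numbers. Timing assignment is concealed by numbered, sealed envelopes: after enrollment, "a designated study staff member will obtain the next randomization envelope in sequence". The envelope discloses the timing arm together with the randomization number, which this section equates with the bottle identification number.

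**Dispensing (6.3, 6.4).** Immediate-arm men receive product at the enrollment visit, according to their number in the allocation sequence. Section 6.4 adds: "Each participant will be randomly assigned a unique ID number that corresponds to a pre-labeled, blinded, bottle of study product".

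**Stock on site (11.1).** "The study sites will receive a supply of study products (TDF and placebo) sufficient for the anticipated number of study participants". It must be kept locked, with limited access.

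**Labels.** Section 5.3.1 says: "Each bottle will be labeled with an identification number, the protocol number, administration instructions, expiration date, lot number, and sponsor address". The Blinding subsection of 5.2 says that the participant ID is the only identifier on the bottle. Section 5.1 assigns a participant number at screening consent and gives the site a separate product identifier once eligibility is confirmed.

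**The concern.** Immediate versus delayed is open to everyone once it is assigned, so concealment before assignment is the main protection against selective enrollment on that factor. Section 10.6 makes this contrast over the first nine months the main behavioral safety analysis, and behavioral safety is a primary endpoint (10.2.1).

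The sealed envelopes are meant to provide that concealment. But a number that has a kit of 4 can only be a delayed number. If delayed product were instead held back until near month 9, a gap in the stocked numbers would show the same thing. If bottle numbers also run in envelope order, the store discloses what the envelope hides.

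Staff who know the next assignment have room to act on it. Screening to enrollment may take up to 45 days, and several exclusion criteria rest on investigator judgement. Steering by perceived risk would create a baseline difference between the timing arms that could mimic or mask behavioral disinhibition.

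**Working it through.** **1. Pack-outs against the dispensing schedule.** Inputs from 6.4: 37 tablets first, 68 one month later, then 105 per quarterly visit. Inputs from 5.3.1: 30 tablets per bottle, with dispensing at enrollment, months 1 and 3 and then quarterly (immediate), or at months 9, 10 and 12 and then quarterly (delayed). The last quarterly supply is at month 21.

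- Delayed, 4 quarterly supplies (months 12 to 21): 37 + 68 + 4 × 105 = 525 tablets; 525/30 = 17.5, rounded up to 18 bottles. The protocol's own figure is 7 + 7 + 4 = 18, so it is reproduced.
- Immediate, 7 quarterly supplies (months 3 to 21): 37 + 68 + 7 × 105 = 840 tablets; 840/30 = 28 bottles = 4 kits of 7. The count of 4 kits is inferred, not stated.

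The kit of 4 therefore occurs only in the delayed arms, and the totals differ (28 against 18).

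**2. What the blocks alone reveal.** A block of 8 holds m = 4 immediate and m = 4 delayed numbers. Someone who tallies past assignments and guesses the timing arm with more places left is correct in an expected share of

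[m + 2^(2m−1)/C(2m, m) − 1/2] / (2m) = [4 + 128/70 − 0.5]/8 = 5.329/8 = 66.6%.

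The share known with certainty, because one arm is used up, is 1/(m + 1) = 1/5 = 20%.

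**3. What readable stock would add.** If the pack-out is visible by number and numbers follow envelope order, the share known is 100% at any block size. Larger blocks lower only the figure in step 2 (62.8% at block size 16, 59.6% at 32), so changing the block size would not close this route.

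**4. Do bottle numbers follow envelope order?**

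- Pointing to yes: 5.2 builds its blocks from study numbers and makes the randomization number the bottle number; 6.3 dispenses by the number in the allocation sequence.
- Pointing the other way or silent: 5.2 discloses the bottle number only when the envelope is opened; 5.1 gives the site the product identifier only after eligibility; 6.4 calls the ID randomly assigned.

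No section settles it. The label texts do not fit together either: a number given at screening consent cannot already be on pre-labeled bottles unless the two numbers are linked in some way that is not described.

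**5. Illustration of the bias (all inputs assumed).** Suppose half the candidates have a 40% and half a 16% chance of reporting a behavior, mean 28% as in 10.6. If a fraction f of slots were steered perfectly by risk, with no adjustment, the bias would be f × (40 − 16) points: 2.4 points at f = 10% and 6 points at f = 25%. The comparison is powered for 12 points. Nothing in the protocol indicates what f would be.

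**The case against.** The strongest objection is that the decisive link is inferred. The envelopes are numbered in sequence, but no section says that bottle numbers are. If the bottle number simply matched the envelope number, there would be little need to disclose it inside. With scrambled numbers, stock would show which arm a number belongs to but not who receives it next. This stands, and it makes the point conditional.

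Three further objections also stand in part.

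- Kits might be shipped in stages. A first kit of 7 looks the same for every number, and the kit of 4 could arrive later.
- Product is locked away with limited access and handled by a designated person, so enrolling staff may never see it. The protocol does not, however, say that stock handlers and enrolling staff are different people.
- Baseline risk behavior is collected by ACASI at enrollment, so a gross imbalance in measured behavior would be visible.

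A reader might go further and infer that staff will know every assignment, or that concealment has failed. The documents do not support that: it needs sequential numbering, distinguishable stock on site before allocation, and access by enrolling staff, and the first and third are not stated. Nor is the TDF/placebo blind exposed, since active and placebo share the same pack-out within each timing arm.

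**Conclusion.** The point holds as a conditional weakness in allocation concealment. Packaging differs by timing arm, the bottle number is the randomization number, and the protocol does not say that bottle numbers are independent of envelope order; its wording leans toward their following it. On that reading, up to 100% of timing assignments could be read from unallocated stock, against about 67% guessable and 20% certain from the blocks alone. The 100% is an upper bound, and the bias figures are illustration only. The risk is confined to the immediate-versus-delayed behavioral comparison. It is a cheap improvement worth making, not evidence that the comparison is invalid.

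**What to change.** In 5.2 and 5.3.1:

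- State that bottle and kit numbers are assigned in an order independent of the envelope sequence, and that each number is disclosed only inside the sealed envelope.
- Reconcile 5.1, 5.2 (including Blinding), 5.3.1 and 6.4 on which number is on the label and when the site learns it.

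The cost is a scrambled number list, to be maintained by the statistician and the manufacturer, and a kit look-up at dispensing. Sample size, visits and analysis do not change.

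Making the packs identical is not the better route. Every man would need 28 bottles, which is 28 − 18 = 10 spare per delayed-arm man, or about 2,000 over the 200 men in the two delayed arms. Three kits of 7 for the delayed arms would still differ from the four implied for the immediate arms.

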## Excluded Concomitant Medications

The following medications are excluded while participating in the study:

- Nephrotoxic agents
  - aminoglycoside antibiotics
  - intravenous amphotericin B
  - cidofovir
  - cisplatin
  - foscarnet
  - intravenous pentamidine
  - other agents with significant nephrotoxic potential
- Probenecid
- Metformin
- Systemic chemotherapeutic agents (i.e., cancer treatment medications)
- Chronic systemic corticosteroids
- Interleukin‑2 (IL‑2)
- Other immunosuppressive/immunomodulatory agents
- Experimental or investigational agents
- Antiretrovirals (other than PEP, see 6.6.1)
- Radiation therapy

Should participants need to start treatment with any excluded concomitant medication, study product will be discontinued. In instances where an excluded medication is initiated prior to study product discontinuation, the investigator must notify CDC and the medical monitor as soon as they are aware of the use of the excluded medication.

# MAIN STUDY PROCEDURES (PART A)

The study procedures to be conducted for each participant enrolled in the main study (Part A) are presented in Tables 1 and 2 (Appendix 3) and detailed in the text that follows. Participants who become HIV-I infected during the course of the study will be asked to continue under a separate visit schedule, referred to as Part B, presented in Table 3 (Appendix 3) that will be covered in Section 7. All routine laboratory specimens will be sent to local institutional laboratories for analysis. Other laboratory specimens will be sent to a designated central lab for analysis or storage.

Any deviation from protocol procedures should be noted in the Case Report Forms (CRFs) or the participant file and the CDC or Contract Research Organization (CRO) should be notified depending on the nature of the deviation.

## Recruitment

Participants will be followed for 24 months. Recruitment will be done using a variety of previously approved and successful recruitment techniques, e.g. outreach, the internet, referrals, etc. Persons will be provided with a brief description about the study and receive pre-screening to determine their interest in the study and potential eligibility. Potential participants will be referred to the clinic site for study screening.

Given the long duration of the study, it may be necessary at times to re-assess recruitment strategies. To inform the development and refinement of optimal recruitment methods targeted focus groups including members and opinion leaders of the community likely to be eligible for enrollment in the trial may be convened. These focus groups will be carried out according to the brief protocol described in Appendix 11.

## Screening Evaluation

Screening evaluations will be used to determine the eligibility of each candidate for study enrollment. To be eligible for study enrollment, participants must meet the study eligibility criteria including testing negative for HIV-1 antibodies by commercially available, FDA approved, rapid whole blood HIV-1 EIA. Candidates who fail to meet eligibility criteria by screening evaluations may be re-screened within 45 days of the initial screen if there is a reasonable expectation that the candidate will be eligible after repeat screening. The interval between the screening evaluation and enrollment must not exceed 45 days.

The following procedures and evaluations are to be completed at the screening visit.

Educational Component and Informed Consent

Each potential study candidate presenting for a screening evaluation will first receive a staff-administered educational flip-chart briefing them about the study (Appendix 4) and be given the opportunity to ask questions. Persons interested in participating in the study must then sign a standardized informed consent form (Appendix 5) indicating that they understand what is being asked of them and permitting the collection of epidemiologic data and specimens for clinical laboratory testing before receiving any further screening procedures.

Comprehension Test

Following the educational component and informed consent, potential participants will then be given a brief comprehension test (Appendix 6). Participants will be required to correctly answer all questions before they can be considered eligible for the trial. Potential participants will be given two opportunities to pass the comprehension test before being excluded from enrollment. The test will be administered, and subsequently staff will review the answers and messages with the potential participant. If, in the staff member’s judgment, the participant has a reasonably good grasp of key study concepts and incorrect answers reflect fairly minor misunderstandings, the test can be re-administered the same day. If in the staff member’s judgment, the participant does not appear to grasp key concepts and incorrect answers reflect serious misunderstandings, the participant will receive additional study education and be asked to return on another day for the comprehension test to be re-administered. Once participants completed the informed consent procedures and comprehension test they will be administered the following assessments to establish their study eligibility.

Epidemiologic/Behavioral Assessment

- Screening Form

Clinical Assessment

- Baseline Medical History Form
- Symptom-directed Physical Exam

*Laboratory Assessment*

- Hematology profile (complete blood count [CBC] with differential and platelet count)
- Chemistry profile: albumin, alkaline phosphatase, alanine transaminase (ALT), aspartate aminotransferase (AST), blood urea nitrogen (BUN), calcium, chloride, creatinine, carbon dioxide, direct bilirubin, gamma-glutamyl transpeptidase, glucose, phosphorus, potassium, sodium, total bilirubin, total cholesterol (non-fasting), total protein, uric acid.
- Serum amylase
- Urinalysis
- HIV-1 whole blood rapid EIA
- Hepatitis B surface antigen (HBsAg).
- Rapid plasma regain (RPR)

*HIV risk reduction counseling and testing*

All potential participants will receive standardized pre- and post-test risk reduction counseling and HIV testing by a FDA-approved commercially available whole blood rapid EIA. Reactive rapid HIV test results must be confirmed with both another FDA approved EIA and Western blot (WB) or immunofluorescent assay (IFA). If confirmatory testing yields negative or indeterminate results, follow-up testing should be performed on a blood specimen collected 4 weeks after the initial reactive rapid test result (53).

